#### 4.1 Inclusion Criteria

- Acute leukemia and MDS patients with detectable MRD,  $\geq 10^{-4}$  of BCR-ABL/ABL ratio, or MC in PB or BM samples obtained during monitoring for relapse after allogeneic stem cell transplantation.
- Detectable MRD, or  $\geq 10^{-4}$  of BCR-ABL/ABL ratio .
- Acute leukemia and MDS patients with MC  $\geq 1\%$  of autologous signals in PB samples confirmed by another PB or BM sample within one week. Patients with MC  $\geq 1\%$  of autologous signals in CD33+ and/or CD34+ subpopulations in PB samples confirmed by BM analyses within one week. Acute leukemia and MDS patients with MC  $\geq 1\%$  of autologous signals including signals in CD33+ and/or CD34+ subpopulations in BM samples.
- Patients without immunosuppressive agents and steroids.
- Patients without chemo- or immune therapy, except patients with tyrosine-kinase inhibitors (TKI) for treatment of BCR-ABL positive leukemias.
- Patients with < grade II GvHD.
- Patients with Karnowsky or Lansky performance status  $\geq 50\%$ .
- Patients and/or his/her legal representative having reviewed the patient information/informed consent form and have had their questions answered and have given written informed consent.

#### 4.2 Exclusion Criteria

- Acute leukemia and MDS patients with hematologic relapse < day 120 after allogeneic stem cell transplantation.
- Acute leukemia and MDS patients with more than 5% malignant cells in bone marrow analyses.
- Patients with immunosuppressive agents or steroids.
- Patients with chemo- or immune therapy, except patients with tyrosine-kinase inhibitors (TKI) for BCR-ABL positive leukemias.
- Patients with  $\geq$  grade II GvHD
- Patients with Karnowsky or Lansky performance status < 50%.
- Patients and/or his/her legal representative having reviewed the patient Information/informed consent form and have had their questions answered and have not given written informed consent.
- HIV-positive patients
- HBV/HCV patients
- Patients with prior solid organ transplantation
- Patients treated with any other investigational product within the last 28 days or five half-lives (whichever is longer).
- Hypersensitivity to any component of the study drug
- Female patients of child-bearing potential not agreeing to use a highly effective method of birth control resulting in a low failure rate (i.e. < 1%) when

used consistently and correctly.

- Male patients with female partners of childbearing potential not agreeing to use a highly effective method birth control resulting in a low failure rate (i.e. < 1%) when used consistently and correctly.
- Pregnancy/Breastfeeding
- Patients with severe infections or signs/symptoms of infection within 2 weeks prior to study start.

### **4.3 Allowed/prohibited concomitant therapies**

Except for patients with BCR-ABL positive leukemia, no concomitant anti-neoplastic treatment is allowed. In the BCR-ABL positive leukemia patients tyrosine kinase inhibitors (TKI) are the standard treatment to control the disease. However, there is no cure possible with TKI as single treatment. As a consequence, these patients may be included into the study while receiving TKI during the CIK cell treatment.

In all other patients' concomitant antineoplastic therapy is not allowed. Antineoplastic chemotherapy however, is necessary to bring patients, with frank hematological relapse after allogeneic stem cell transplantation, in complete hematological remission (<5% of leukemia blasts in the bone marrow). Patients with molecular relapse who are still in hematological remission are eligible for this study.

All chemotherapy given for remission induction is not part of the study. Chemotherapy has to be stopped 3 days before CIK cell infusions could be given.

## **5 Investigational Medicinal Product - CIK cells**

### **5.1 CIK Cell Donors**

CIK cells are generated from PBMCs of original stem cell donors after written informed consent.

### **5.2 Donor Exclusion Criteria**

- Positive for HIV, HBsAG, HBc, HCV, TPHA
- Contraindication for blood withdrawal
- Pregnancy or breast feeding
- Heart disease
- Myocardial infarction < 3 months
- Seizure disorder
- mental health problem
- Malignant diseases

### **5.3 CIK Cell Generation**

CIK cells are expanded according to GMP-terms from PBMCs of original stem cell donors by addition of interferon IFN $\gamma$ , activating antibody directed against CD3, IL-2 and IL-15.

### **5.4 CIK Cell Recipient**

Patients with molecular relapse without aGvHD  $\geq$  grade II can be included and will receive CIK cell infusions in increasing doses.

Starting dose of  $1 \times 10^6$  CD3 $^{+}$ CD56 $^{-}$  CIK cells/kg recipient body weight will be increased in intervals of 4-6 weeks to  $5 \times 10^6$  CD3 $^{+}$ CD56 $^{-}$ , and  $1 \times 10^7$  CD3 $^{+}$ CD56 $^{-}$  CIK cells/kg. Patients will be screened for relapse and signs of GvHD according to GSC. Relapsed patients will be censored. Patients who experience disease progression or  $<$  grade II aGvHD may receive modified CIK cell doses. No further CIK cell infusions will be administered in the presence of aGvHD  $>$  grade II.

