## **2.4 Secondary Endpoints**

- Molecular response as efficacy end point.
- Progression free survival at 1 year after initiation and the end of CIK cell therapy.
- Overall survival will be assessed 1 year after initiation and the end of CIK cell therapy.

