### **3.3 Study Duration**

The estimated duration of the recruitment period will be 3 years and the total duration of the study is expected to be at least 5 years.

The study duration per patient will include study phase during CIK cell infusions and observational phase after the last CIK cell infusion.

Study phase will last until the patient reaches molecular remission (= end of CIK cell infusions), progresses or until the patient has received a maximum of 8 CIK cell infusions (maximum duration of study phase 1 year).

Observational phase will last 1 year after the last CIK cell infusion.

Additionally, CIK cell infusions will be terminated if the patient meets discontinuation criteria (see chapter 8.1). "Off-protocol" patients will be followed up for another 28 days. Patients where CIK cell infusions are discontinued, but who stay in the protocol will be followed up for 1 year (see chapter 8.1).

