**The following criteria lead to withdrawal from study; patients will be followed up for one month:**

- Pregnancy of female patients
- Relapse of the underlying disease during CIK cell treatment requiring other treatment (e.g. systemic chemotherapy, second stem cell transplantation)

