## Analysis

A descriptive statistics will be performed at the end of the study. An intent-to-treat principle (ITT) or per-protocol analysis will be done.

To analyze the efficacy of CIK cell treatment following factors will be considered:

- Complete and partial molecular response
- rate and duration of complete/partial molecular response following CIK cell administration at the end of CIK cell infusions and after 1 year of first CIK cell infusion
- rate of and time to non response
- rate of and time to relapse with previous partial/complete response
- Progression-Free survival (PFS) and overall survival (OS)
- Cumulative incidences of: haematological relapse/progression, deaths without relapse/progression
- Cumulative incidence of aGVHD > grade II and extensive chronic GvHD
- Median and range for the number of CIK cell dose and for cumulative dose CIK cells/kg for all patients, children and adults

- Median and range for cumulative T cells/kg according donor type (MSD, MUD,MMFD) that patient requires in the study

Complete molecular response is defined as the molecular remission: the Minimal Residual Disease not detectable (MRD < 10^-6) and Mixed Chimerism MC < 1%.

Partial response is defined as no molecular remission but not haematological relapse. Non response is defined as haematological relapse without previous or complete response.

The median of PFS and OS time will be estimated. Kaplan-Meier estimates will be used to estimate PFS probability and OS probability. Log-rank test will be used as appropriate. For PFS will be considered as events: disease progression or relapse, death without relapse/progression and secondary neoplasm. For OS death from any cause will be considered an event.

Gray-Model will be used for cumulative incidences. Patients lost to follow-up without event will be censored at the date of their last follow up evaluation.

PFS, OS and cumulative incidences will be estimated after 1 year initiation of CIK cell therapy and after 1 year until the last CIK cell infusion.

If the data meet the necessary requirements, longitudinal analysis will be conducted to explore the improvement of hematologic and immune reconstitution of leucocyte, CD3-, CD4-, CD8-, CD56-, and CD14-positive cells until the first year after begin of the CIK cells therapy.

The dynamic of cytokine profile during cell infusion and tumor escape mechanisms following CIK cell infusion will exhibit in curves over the time.

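### Section 5.4 censors relapse, which section 11 counts as a PFS event; separately, follow-up that ends about a month after on-treatment relapse biases overall survival upward

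*Protocol*

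**What the plan says.** **Relapse.** In section 5.4, among the dosing and GvHD screening rules, the protocol says "Relapsed patients will be censored". Section 11 (Analysis) says "For PFS will be considered as events: disease progression or relapse, death without relapse/progression and secondary neoplasm". It also plans rates of and times to relapse, and a cumulative incidence of haematological relapse or progression.

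**Follow-up after relapse.** One criterion for leaving the study in section 8.1 is "Relapse of the underlying disease during CIK cell treatment requiring other treatment (e.g. systemic chemotherapy, second stem cell transplantation". The heading of that list is "The following criteria lead to withdrawal from study; patients will be followed up for one month". Section 3.3 says that off-protocol "patients will be followed up for another 28 days". By contrast, patients whose infusions stop but who stay in the protocol are followed for 1 year.

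**Endpoints.** Section 2.4 lists "Progression free survival at 1 year after initiation and the end of CIK cell therapy" and "Overall survival will be assessed 1 year after initiation and the end of CIK cell therapy". Section 11 adds "For OS death from any cause will be considered an event", uses Kaplan-Meier, and censors patients lost to follow-up without an event at their last evaluation.

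**The concern.** There are two separate defects.

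1. Relapse cannot be both a censoring reason and an event for the same endpoint. Section 5.4 names no endpoint and uses a term with a fixed meaning in survival analysis, so an analyst could apply it to PFS.
2. The OS definition needs a death date, or confirmed survival, for every patient up to the 1-year time points. For patients withdrawn after on-treatment relapse, the protocol asks for about one month of data. Kaplan-Meier assumes that censored patients have the same later risk as those who stay under observation. Patients censored because they relapsed do not: sections 1.1, 2 and 5.5 call relapse the major cause of treatment failure, with about a 20% chance of cure from a second transplant and under 15% success with donor lymphocytes.

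At stake are the PFS and OS estimates that would inform any later, larger study. The PFS wording can be settled at any time before analysis. Death dates that were never requested cannot be recovered by an analysis plan.

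**Working it through.** The protocol states no PFS or OS rate, so there is no figure to reproduce. The check compares the passages and then sizes the effect under stated assumptions.

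**Step 1: who falls under the one-month rule.** Responders stop infusions and stay in the study (8.1). Patients without molecular remission can receive 8 infusions 4 to 6 weeks apart (3.1). That is 7 intervals, so 7 × 4 = 28 to 7 × 6 = 42 weeks from first to last infusion. Patients who have not responded can therefore be exposed to the rule for much of the first year. Relapse in the observational phase is outside it.

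**Step 2: assumptions, none of them from the protocol.**
- Constant, independent hazards; secondary neoplasm ignored.
- 1-year death without relapse 10%: λd = −ln 0.90 = 0.105 per year.
- 1-year relapse r = 30%, 50% or 70%: λr = −ln(1 − r).
- Median survival after relapse m = 3, 6 or 12 months: μ = ln 2 / (m/12).
- Half or all of relapsed patients withdrawn and censored 28 days after relapse: δ = 28/365.25 = 0.0767 years.

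**Step 3: PFS.** With relapse as an event, 1-year PFS = 0.90 × (1 − r):
- r = 30%: 0.90 × 0.70 = 0.63
- r = 50%: 0.90 × 0.50 = 0.45
- r = 70%: 0.90 × 0.30 = 0.27

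With relapse censored, only λd remains and Kaplan-Meier gives 0.90 in all three cases, 27 to 63 points higher.

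**Step 4: OS, worked for r = 50% and m = 6 months.** λr = 0.693, h = λr + λd = 0.799, μ = 1.386, μ − h = 0.588.

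True 1-year OS = e^(−h) + λr(e^(−h) − e^(−μ))/(μ − h) = 0.450 + 0.693 × (0.450 − 0.250)/0.588 = 0.450 + 0.236 = 0.686.

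If all relapsed patients are withdrawn, the only relapsed patients still at risk after day 28 are those who relapsed within the previous 28 days. Per relapse-free patient their number is R = λr(1 − e^(−(μ − h)δ))/(μ − h) = 0.052. The hazard that Kaplan-Meier sees is (λd + μR)/(1 + R) = (0.105 + 1.386 × 0.052)/1.052 = 0.169. The first 28 days add a cumulative hazard of 0.0106. Estimated OS = exp(−(0.0106 + 0.923 × 0.1686)) = 0.847, which is 16 points too high. If half are withdrawn, the same method gives 0.752, 6.6 points too high.

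**Step 5: all scenarios** (same formulas; simulation with 400,000 patients per scenario agrees to within 0.002).

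| Relapse | Median after relapse | True OS | Half withdrawn | All withdrawn |
|---|---|---|---|---|
| 30% | 3 months | 0.718 | 0.776 | 0.845 |
| 30% | 6 months | 0.777 | 0.820 | 0.872 |
| 30% | 12 months | 0.831 | 0.856 | 0.887 |
| 50% | 3 months | 0.586 | 0.675 | 0.798 |
| 50% | 6 months | 0.686 | 0.752 | 0.847 |
| 50% | 12 months | 0.779 | 0.817 | 0.875 |
| 70% | 3 months | 0.441 | 0.547 | 0.732 |
| 70% | 6 months | 0.583 | 0.662 | 0.811 |
| 70% | 12 months | 0.719 | 0.766 | 0.857 |

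The overstatement runs from 2.5 to 11 points with half withdrawn and from 6 to 29 points with all withdrawn. The sign never changes, because the death rate after relapse exceeds that before it in every scenario: even at a 12-month median, μ = 0.693 against λd = 0.105.

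**The case against.** The strongest reply on PFS is that section 11 is the statistics section, defines the event explicitly and plans relapse analyses that would be empty if relapse were censored. The sentence in 5.4 may simply mean that the patient leaves the infusion schedule. This stands as far as it goes. A reader might infer that the trial's PFS is biased, but the documents show only a contradiction. The bias arises only if 5.4 is allowed to override section 11, and if section 11 governs, the one-month cut does not harm PFS.

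On OS, the reply is that the rule is narrow: relapse during CIK treatment, and only if other treatment is required. That also stands. A reader might infer that every relapsed patient is lost after 28 days, but section 3.3 keeps patients who remain in the protocol under follow-up for 1 year, and later relapses are not caught. The all-withdrawn figures are therefore a ceiling.

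It can also be said that PFS and OS are secondary endpoints in a study declared exploratory, and that its precision tables concern molecular response and GvHD. This limits the severity but does not close the gap. Section 8.1 asks for a final evaluation at withdrawal and for observations to be completed as far as possible. No section asks for survival status of withdrawn relapsed patients after the month ends.

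**Conclusion.** Both parts hold, with different force. Sections 5.4 and 11 contradict each other on relapse; the 27 to 63 point effect on PFS is conditional on 5.4 being applied. The OS defect does not depend on 5.4. For patients withdrawn after on-treatment relapse requiring other treatment, follow-up ends because of a poor prognosis, and the Kaplan-Meier estimate is too high.

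The direction follows from the protocol's own rules and its account of relapse. The size does not: 2.5 to 11 points (half withdrawn) and 6 to 29 points (all withdrawn, upper bound) rest on assumed relapse, non-relapse mortality and post-relapse survival rates. A reader might go further and call the OS analysis invalid. The documents support only an upward bias of unknown size.

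Severity is moderate, since these are secondary endpoints in an exploratory study. The correction is still needed before patients leave follow-up, because the lost survival data cannot be restored by analysis.

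**What to change.** 1. Delete or reword the sentence in section 5.4 so that it agrees with section 11: relapse or progression is a PFS event at its date.
2. Amend sections 8.1 and 3.3 so that vital status and date of death are collected for all treated patients, including those withdrawn for relapse, up to the 1-year OS time points. Routine post-transplant follow-up can supply this. State one duration where the text now gives both one month and 28 days.
3. State in section 11 that deaths after relapse count in OS whether or not the patient has been withdrawn.

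No change to treatment, to the stopping rules or to the time origin is needed; estimates from the start of therapy are already planned.

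The cost is a short amendment, one sentence in the consent form and a status check per withdrawn patient. Reported OS will be less favourable than under the present rule.

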Starting T cell dose within CIK cell infusions was 1x10^6 T cells/kg body weight. Regardless of donor type, dose escalation continued up to 1x10^8 T cells/kg body weight if no signs of acute GvHD >grade I occurred. Median doses of infused T cells were 6x10^7 in the matched unrelated and 1x10^7/kg in the haploidentical transplantation setting. Mild signs of acute GvHD occurred in 2 patients (14%).

Another 3 patients (21%) developed acute GvHD grade III with evidence of cutaneous, intestinal and hepatic involvement. All of these high-risk patients had been treated with CIK cells from haploidentical donors prophylactically at a maximum dose of 5x10^6, 5x10^6 and 20x10^6 CD3+CD56 CIK cells/kg body weight. All patients experienced a timely coincident regeneration of CD3+ T cells. Therefore it is not clear whether the occurrence of GvHD is solely attributable to CIK cell infusions. Treatment for acute GvHD included immunosuppressive medications in addition to steroid therapy and infusions of mesenchymal stroma cells. One patient additionally received extra corporal photopheresis. All patients finally recovered from GvHD and remained in complete remission until the last follow-up.

In 6 patients (43%), 3 with overt and 3 with impending relapse, CIK cell infusions temporarily provided stable disease (median 218 days, range 56-563 days), followed by another allogeneic SCT in 2 cases. Deaths of 2 heavily pretreated AML-patients (14%) who remained in remission after CIK cell infusions were not CIK cell-related. Another 6 leukemia patients (43%), 3 of whom were not in remission at the time of SCT, are still in complete remission. All of them were offered CIK cell infusions from haploidentical donors.

Accordingly, Introna, Laport, Linn and colleges described application of donor-derived CIK cells in adult patients with relapsed hematological malignancies after allogeneic SCT. Altogether, serial CIK cell infusions seem to be a promising therapeutic approach for patients being at risk of relapse, provided that CIK cells are administered in high numbers and short-term intervals, early after allogeneic SCT.

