## **3 Study Design**

This is a phase I/II study to investigate the feasibility, safety and efficacy of IL-15 activated CIK cells in patients with acute leukemia or MDS showing evidence of molecular relapse after allogeneic SCT.

- CIK cell infusions will be given with an interval of 4-6 weeks according to a dose escalation schedule in patients with impending relapse after allogeneic SCT. In presence of aGvHD  $\geq$  grade II, the next scheduled infusion will not be administered. CIK cell infusions will be administered until the patient reaches molecular remission, until a maximum of 8 infusions are reached or until the patient progresses, provided that patients develop no more than grade I aGvHD.

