- CIK cell infusions will be given within a minimum of 4 and a maximum of 6 weeks between infusions provided that signs of acute GvHD (aGvHD) remained below grade II aGvHD. Second CIK cell dose will be  $5 \times 10^6$  CD3+CD56 CIK cells/kg in pediatric and adult patients. Third CIK cell infusion and all following infusions will include  $1 \times 10^7$  CD3+CD56 CIK cells/kg in pediatric and adult patients. CIK cell infusions will be administered until the patient reaches molecular remission, provided that patients develop no more than grade I aGvHD.

If the patient does not reach molecular remission, administration of CIK cell infusions will be stopped after the 8th CIK cell infusion, maximal duration of the study phase is one year.

(For "Criteria for Discontinuation of the Treatment or Premature Withdrawal of the Patient" please also see chapter 8.1).

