### **Follow up 1-2 weeks after CIK cell infusions**

Before, one hour, one and two weeks after CIK cell infusion the patients will be monitored for immune responses. Therefore 7.5 – 10 mL of EDTA blood will be taken at above mentioned time points for assessment of blood counts, numbers of CD3-, CD4-, CD8-, CD56-, CD14-positive cells, cytokine release and tumor escape mechanisms. Blood samples will be gathered by stem cell laboratory:

University Hospital Frankfurt, Goethe University  
Department for Children and Adolescents  
Division for Stem Cell Transplantation and Immunology  
Stem Cell Laboratory (House 32D)  
[name]  
[contact], [contact]

**Follow up 2-4 weeks after CIK cell infusions** (CIK cell infusions will be continued until patient reaches molecular remission, until a maximum of 8 infusions are reached, until the patient progresses or discontinuation criteria are met):

- History taking\*
- Physical examination\*
- Karnowsky/Lansky performance index\*
  
- Body weight\*
- Peripheral blood
  - Blood count\*
  - Bilirubin\*
  - Chimerism (monthly\*)
- Bone marrow (every 3 months\*)
  - Morphology or histology
  - Chimerism, including subpopulations if appropriate
  - MRD if appropriate
  - BCR-ABL/ABL ratio if appropriate

\* Obligatory

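### Section 5.4 allows undefined modified CIK cell doses after disease progression, while sections 3, 3.2 and 3.3 end infusions or the study phase there, and progression is not defined

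*Protocol*

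**What the plan says.** Four places in the protocol govern infusions after progression.

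- Section 3 (Study Design) gives infusions until molecular remission, until 8 infusions, "or until the patient progresses, provided that patients develop no more than grade I aGvHD".
- Section 3.2, in the follow-up 2 to 4 weeks after an infusion, continues infusions until remission, 8 infusions, or "until the patient progresses or discontinuation criteria are met".
- Section 3.3 ends the study phase, which is the infusion phase, when the patient reaches molecular remission, "progresses or until the patient has received a maximum of 8 CIK cell infusions".
- Section 5.4 has a sentence that opens "Patients who experience disease progression or" and, after a less-than sign, ends "grade II aGvHD may receive modified CIK cell doses".

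The dose schedule is in section 3.1: 1 x 10^6 CD3+CD56- cells/kg, then 5 x 10^6. "Third CIK cell infusion and all following infusions will include" 1 x 10^7 cells/kg. Section 5.4 repeats these three steps.

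Section 8.1 has two lists. The first stops infusions but keeps the patient in the study: GvHD above grade II, response, severe infection. The second withdraws the patient with one month of follow-up: pregnancy, or relapse during treatment that needs other therapy.

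**The concern.** Sections 3 and 3.2 leave a patient who progresses with no further infusions. Section 5.4 lets the same patient receive more, at a dose altered in an unstated way. An investigator who reads one section stops, and one who reads the other may continue.

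These are dosing and stopping rules in a dose-escalation trial in children and adults whose primary endpoint is dose-limiting grade III or IV acute GvHD, so they cannot be left to an analysis plan. If sites act differently, the dose behind each GvHD observation differs for reasons outside the schedule. The number of infusions and the cumulative cells/kg that section 11 summarises would then mix two policies. Progression is also a PFS event in section 11, so treatment might continue after an efficacy event in some patients and stop in others.

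**Working it through.** The protocol gives no figure to reproduce for this point. The check sets the rules side by side.

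| Section | Rule at progression | Dose stated |
|---|---|---|
| 3 | Infusions end | Refers to the escalation schedule |
| 3.1 | Progression not mentioned; infusions end at molecular remission or after the 8th | 1, 5, then 10 x 10^6/kg |
| 3.2 | Infusions end | None |
| 3.3 | Study phase ends | None |
| 5.4 | Modified doses allowed | Same three steps; modified dose not defined |
| 8.1, stop list | Progression not listed | None |
| 8.1, withdrawal list | Only relapse needing other treatment | None |
| Schedule footnote 7 | Progression not named; refers to remission and discontinuation criteria | None |

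**Step 1: does any section decide between them?** Only in part. The 8.1 withdrawal list fixes the outcome for relapse that requires other treatment: the patient leaves the study. A patient who progresses without needing other treatment is on neither 8.1 list, so 8.1 does not choose between section 5.4 and sections 3, 3.2 and 3.3. The eligibility conditions for the next infusion in section 3.2 concern only immunosuppression, steroids and chemo- or immune therapy.

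**Step 2: is progression defined?** No. All patients enter with molecular relapse, so progression must mean something beyond that, but the protocol does not say what. Section 11 defines complete, partial and non-response but not progression. It places progression beside relapse both in the PFS events and in the cumulative incidences.

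**Step 3: is the modified dose defined?** No section gives its size, direction, trigger or decision-maker.

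**Step 4: how far can the two readings diverge?** As an illustration, take a patient who progresses after the third infusion.

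- Cumulative dose at that point: 1 + 5 + 10 = 16 x 10^6/kg. Under sections 3 and 3.2 it stays there.
- Infusions left before the maximum: 8 - 3 = 5.
- If section 5.4 were followed and each of those were given at the top step: 16 + 5 x 10 = 66 x 10^6/kg, a difference of 50 x 10^6/kg.

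The top step is used here only because it is the largest dose the protocol states. The actual modified dose is unknown, so this shows how much room the text leaves and does not estimate what would be given.

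**The case against.** The best defence is that section 5.4 uses progression in a narrower sense. The sentence just before it deals with relapsed patients separately, by censoring them. Since everyone enrols with molecular relapse, progression in 5.4 could mean rising MRD or chimerism short of haematological relapse, while sections 3, 3.2 and 3.3 could mean overt relapse. On that reading the rules are compatible. This stands as a possible intention, and it means a reader should not infer that the sections are irreconcilable under every reading. It does not repair the text, because the protocol never separates the two uses.

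A second defence is that section 8.1 already handles the serious case. It does so for relapse that needs other treatment. A reader might infer that every progressing patient could be handled either way, and that is too broad.

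A third is that modified may mean reduced. A reader might infer a licence for doses with no upper limit, but the text does not say that: 5.4 itself lists steps ending at 1 x 10^7/kg, and 3.1 keeps that dose for all later infusions. What can be said is that the modified dose is undefined.

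The sentence as printed also covers acute GvHD below grade II, for whom section 3.1 gives the scheduled infusion "provided that signs of acute GvHD (aGvHD) remained below grade II aGvHD". That looks like a further conflict, but it rests on one printed sign that may be a slip, so nothing here depends on it.

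**Conclusion.** The point holds as a conflict between stated rules, made worse by two undefined terms. Section 5.4 allows altered dosing after progression, sections 3 and 3.2 stop infusions and 3.3 ends the study phase, and 8.1 resolves only relapse that needs other treatment. It should be fixed, because it decides who is given cells and at what dose in a trial that measures dose-limiting toxicity.

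Its size in patients or in GvHD events cannot be derived: the protocol gives neither an expected number of progressors nor a modified dose. The conclusion assumes only that progression carries its ordinary meaning in all four sections, since no other is given.

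Two stronger inferences are not supported.

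- The grade III cases in section 1.5 do not show that a higher dose after progression raises the GvHD risk. Two of the three had maximum doses of 5 x 10^6/kg, half of this trial's top step. All three had haploidentical donors and prophylactic treatment, and the protocol says attribution to CIK cells is unclear.
- Dosing at progression does not necessarily breach the low-leukaemic-burden rationale in section 1.1. That depends on what progression means, and rising MRD with few blasts would still be low burden.

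**What to change.** 1. In section 5.4, delete the sentence on modified doses and state that infusions end at progression, as in sections 3, 3.2 and 3.3.
2. In section 8.1, add progression not requiring other treatment to the list that stops infusions while the patient remains in the study. Keep relapse requiring other treatment in the withdrawal list. The two must stay separate: adding progression to the first list without that qualifier would assign some patients both to one year of follow-up (section 3.3) and to withdrawal with one month.
3. If the intention is to treat through rising MRD or chimerism short of haematological relapse, do not delete the sentence. Define that state, say who may receive a modified dose and what the dose is, cap it at 1 x 10^7 CD3+CD56- cells/kg, and amend sections 3, 3.2 and 3.3 to match.

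The cost is protocol amendment wording, with the approvals in section 7.7 if the amendment counts as substantial. The sample size and planned analyses do not change. Follow-up of progressing patients who stay in the study would be the one year that section 3.3 already gives to patients whose infusions are stopped but who remain in the protocol.
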